## Methods

The word clouds were generated working with Myelopathy Support, an online peer-to-peer support community for individuals with DCM and their caregivers. Ethical approval has not been required for the involvement of the Myelopathy Support members as their role is to help to develop the word clouds for the survey and they are not research participants. The moderator for the Myelopathy Support group is a member of the Steering Group for the Priority Setting Partnership who design and manage the survey. Myelopathy Support is an arm of Myelopathy.org, an international charity for DCM. Myelopathy Support includes an online support group hosted on Facebook (California, USA). The group is closed, and access is moderated by Myelopathy.org volunteers [IS]. Individuals wishing to join the group are required to confirm they have myelopathy and will adhere to community guidelines. Prior experience has demonstrated that demographics and disease characteristics of this group, aside from a female gender predominance, are broadly representative of DCM [18–22].

Over a 2-week period, four posts were pinned to the top of the Myelopathy Support group: (1) “What words do you associate with diagnosis phase of myelopathy?” (2) “What words do you associate with the management phase of myelopathy?” (3) “What words do you associate with the long-term care/living with myelopathy?” (4) “Any other relevant words?”. The posts were accompanied by covering information outlining the background and rationale for this exercise, piloted and approved by IS [Supporting Information 1]. In short, group members were encouraged to add their unrepresented suggestions as comments on the particular post or posts and to vote (as likes or with emotions) the posted words with which they agreed. This exercise was moderated by a group administrator [IS]. No data was collected on individual participants, e.g., their demographics. There was no limit on how many times a group member could contribute.

Following the 2-week period, the submitted words and their respective votes were reviewed by the AO Spine RECODE-DCM Management Group [ODM, ES, DK, IS, BMD, OH] and duplicated words were removed. By mutual agreement, words considered to be out of scope were removed, and words felt to be better reflected in a different section were moved. Through consultation with representatives of the other Healthcare Professional stakeholder group (ES, SS) and discussion amongst the management group, some additional word suggestions were put forward. The aim of this was to include the perspective of an additionally under-represented stakeholder group [23] (other healthcare professionals) while ensuring this remained patient-centered by presenting any suggestions back to the group.

The final lists were then re-posted to the group as a series of polls, to allow members to review the list and vote for the words with which they most agreed [Supporting Information 2]. Users could continue to submit additional suggestions, which were then available to be polled. Users could not vote more than once. This second-round exercise ran for a further 2 weeks. The findings were processed by the management group, to combine duplicates and remove out of scope suggestions. Word clouds were generated using WordArt.com (California, USA) for each major section. The size of the word was proportional to the number of votes it received. Words without a vote were not included. The first iteration of the output was used, without modification.

## Results

Members of the Myelopathy Support online group submitted 79 words, specifically 18 for diagnosis, 16 for treatment, 29 for long-term management, and 16 for other. Following internal discussion, with consultation from ES and SK, a further 25 words were suggested for inclusion, including 4 for diagnosis, 8 for treatment, 8 for long-term management, and 5 for other. It was agreed that “Loss of Vision” was out of scope, and “Depression,” “Walking Problems,” “Worry,” and “Anxiety” were already represented in the long-term management and could be removed from the other category. The final shortlist of words is shown in Table 1 and was placed into Facebook polls as outlined in Supporting Information 3 and Supporting Information 4. In this second round, a further 39 words were added. All words were polled at least once, with “weakness” receiving the maximum votes 47 (Table 2). The data was used to generate word clouds for their respective sections (Figs. 1, 2, 3, and 4).

**Table 1 Tab1:**
[figure not shown]
Words and their respective categories, placed into polls for the second stage. Words in green have been moved from treatment to diagnosis. Words in black were submitted by Myelopathy Support members. Words in red were submitted by the management group

**Table 2 Tab2:**
[figure not shown]
Results of polling. Words submitted as new are in red

**Fig. 1 Fig1:**
[figure not shown]
Word cloud for diagnosis

**Fig. 2 Fig2:**
[figure not shown]
Word cloud for treatment

**Fig. 3 Fig3:**
[figure not shown]
Word cloud for long-term management

**Fig. 4 Fig4:**
[figure not shown]
Word cloud for other

## Implementation plan for AO Spine RECODE-DCM

AO Spine RECODE-DCM includes several parallel consensus processes, including a research priority setting partnership and the development of a minimum data set. The AO Spine RECODE-DCM survey will be accessed via a single-entry point, with block randomization to one of the two streams (either Priority Setting Partnership or Minimum Data Set) per stakeholder group (spinal surgeon, other healthcare professionals, persons with DCM and their supporters). This methodology was chosen for efficiency to enable a single recruitment phase. Further detail on the overall process is provided in reference [5].

For participants allocated to the PSP, further 1:1 block randomization will occur to two streams, a survey including word clouds and a second stream without word clouds. For those allocated to the word cloud stream, participants will complete the survey as planned initially. However, after survey completion, respondents will be presented with a brief overview of the development method and aims of the word cloud subproject. Participants will then be presented with each word cloud in turn, with the option to submit further research questions. This approach was taken for two principal reasons. Firstly, to ensure the traditional JLA methodology can be conducted contemporaneously, but still partitioned if required, and secondly, to enable any cross over of responses within the word cloud arm to be considered. Participants will be able to move freely within the survey up until the point they reached a final “thank you” page. Consequently, it will be theoretically possible for participants in the word cloud stream to edit their pre-word cloud form having seen the word clouds. This cannot be tracked by the survey platform. However, by retaining an arm who have no access to the word clouds, any such cross over can be evaluated.

As part of any JLA PSP, the raw suggestions are processed into their individual questions. Then questions deemed “out of scope” are removed, before the remaining questions are collated into common themes, each represented by a summary question. This process is iterative, with a clear audit trail to track where any submission ends up. Consequently, the overall number of questions submitted, alongside the number deemed “in-scope” research questions and the number linked to a summary question appearing in the final research priority list, will be recorded in this evaluation. These numbers will be compared between streams, and for those in the word cloud stream, before and after viewing the word cloud. Metrics will be evaluated overall and per stakeholder group, as well as specifically for each category of question (diagnosis, treatment, long-term management, and other). The impact of the relative size of a word or its relative competition (the number of other words in the cloud) will also be evaluated, by comparing the number of questions generated that match each word and evaluating for a positive correlation. The use of word clouds will be judged meaningful if they prompt a greater breadth of suggestions across the phases of care. Suitable statistical methods will be used for comparisons based on the distribution of the data.

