## Discussion

Primarily driven by individuals with DCM, word clouds were developed for associations with the diagnosis, treatment, long-term phases of care, and an “other” category. These will be nested within AO Spine RECODE-DCM, in order to evaluate their role in supporting the research uncertainty gathering phase of a JLA Research Priority Setting Partnership.

The diagnosis word cloud highlights prominent symptoms and MRI, the gold standard diagnostic tool. The treatment section highlighted the gold standard treatment—surgical decompression. The long-term management section highlighted disability and tiredness. The other category highlighted ignorance of the condition. Amongst several pervasive themes were pain and psychological consequences such as anxiety and depression.

The perspective of PwCM has been limited within DCM research to date, but wider experience from healthcare shows this can bring critical insights [8]. In one of the few previous DCM examples, our evaluation of PwCM recovery priorities identified that pain, alongside upper and lower limb function, was most valued [18]. This contrasts the current outcomes of research studies not including PwCM input and supports the rationale for AO Spine RECODE-DCM, and its establishment of a minimum data set. The broad range of ideas displayed goes beyond current research foci [23] indicating the value of engaging PwCM in research design [8].

We hypothesize that this PwCM perspective could be enhanced within a JLA PSP. While PSP were developed to ensure the voice of patients is incorporated into setting a research agenda, this is only really considered by the group as a whole during the final consensus meeting. Put specifically, professionals do not have the opportunity to reflect on “patient” perspectives until summary questions have already been generated and shortlisted. In this nested methodological study, we will therefore evaluate whether the PwCM generated word clouds can help the group as a whole develop research questions and specifically, priority research questions.

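### No order is stated or randomised for the four word clouds; with one common order, analyses that compare or pool across clouds cannot separate position from phase of care

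*Protocol article*

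**What the plan says.** All references are to the Protocol article, section *Implementation plan for AO Spine RECODE-DCM*, unless stated otherwise.

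- **Randomisation.** Respondents are first allocated to the priority-setting or the data-set survey. Within the priority-setting survey, "further 1:1 block randomization will occur to two streams, a survey including word clouds and a second stream without word clouds". No further randomised factor is described.
- **Delivery.** The word cloud stream first completes the ordinary survey. "Participants will then be presented with each word cloud in turn, with the option to submit further research questions". The page order is not given.
- **Navigation.** "Participants will be able to move freely within the survey up until the point they reached" the closing page.
- **Comparisons.** "These numbers will be compared between streams, and for those in the word cloud stream, before and after viewing the word cloud".
- **Breakdown.** "Metrics will be evaluated overall and per stakeholder group, as well as specifically for each category of question (diagnosis, treatment, long-term management, and other").
- **Word-level analysis.** Questions matching each word are counted and examined for a positive correlation with the word's relative size and with its competition, defined as how many other words share its cloud.
- **Success rule.** "The use of word clouds will be judged meaningful if they prompt a greater breadth of suggestions across the phases of care".
- **Overlap between clouds** (*Discussion*). "Amongst several pervasive themes were pain and psychological consequences such as anxiety and depression".

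**The concern.** Each respondent in the word cloud stream meets four optional pages one after another, having already completed a whole survey. Position can matter in two ways. Later pages may find respondents who are more tired, or fewer of them. And a theme that appears in several clouds may prompt its question at the first appearance, so that the later cloud gets no credit for it.

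If one sequence serves everyone, these effects fall on the same phases for every respondent. A lower yield from a later cloud could then be read as a weaker response to clouds in that phase, when position alone could produce it. The same applies to conclusions about which words, or how crowded a cloud, prompt questions. The aliasing is built in when the survey opens and cannot be undone in analysis.

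**Working it through.** The article gives no sample size, yield or drop-off figure, so there is no stated number to reproduce. The check is which planned contrasts depend on the order of the clouds.

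**1. Between streams, within one category.** The contrast is the mean count in category c with clouds minus the mean count in category c without clouds. Respondents are randomised to the whole four-cloud package or to none. Page order is part of that package, so it does not bias the contrast.

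**2. Before/after yields, compared between categories or credited to one cloud.** Write the expected post-cloud yield of cloud k as a phase effect times a position effect: y(k) = a(k) × p(position of k).

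- With one common order there are 4 observed mean yields. A model with an overall level, 3 phase contrasts and 3 position contrasts has 1 + 3 + 3 = 7 parameters. It cannot be fitted to 4 means.
- The stream without clouds has no corresponding second pass, so it cannot supply the position effect.

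Illustration, with assumptions that are not from the documents: equal phase effects and a constant loss d of active respondents per further page. The ratio of the fourth cloud to the first is (1 − d)³.

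| Assumed loss per page | Calculation | Fourth / first | Apparent difference |
|---|---|---|---|
| 5% | 0.95³ | 0.857 | 14% |
| 15% | 0.85³ | 0.614 | 39% |
| 25% | 0.75³ | 0.422 | 58% |

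If each cloud instead takes each position equally often, the average position factor at 15% loss is (1 + 0.85 + 0.7225 + 0.614) / 4 = 0.797 for every cloud, and the apparent difference disappears. The loss itself remains but is shared equally. Position and phase are then crossed in 4 × 4 = 16 cells, which is enough to fit the 7 parameters.

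**3. Word competition.** How many other words share a cloud is essentially one value per cloud, so there are at most four distinct values. Under one order this variable is aliased with position as well as with category. Varying the order removes position. It does not remove the aliasing with category, because each category still has only one cloud.

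**4. Word size.** Size varies within a cloud, so a correlation calculated inside one cloud holds page position constant. A correlation pooled over the four clouds does not. Carry-over can also act inside a cloud: a word whose theme appeared earlier may score low whatever its size.

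**5. How much overlap remains.** According to *Results*, four words, two of them anxiety and depression, were taken out of the other category before the second poll because long-term management already covered them. A further 39 words were added in that poll, and *Methods* says duplicates were combined afterwards. The *Discussion*, describing the finished clouds, still reports recurring themes ("Amongst several pervasive themes were pain and psychological consequences such as anxiety and depression"). Overlap was therefore reduced but not eliminated.

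**The case against.** The strongest objection is that a fixed order is inferred from silence. The article says only that the clouds come in turn. The sequence in which it lists the categories in prose is not evidence of page order. Page order is a detail that a condensed article may leave to the full protocol, and the article refers readers elsewhere for detail of the overall process. This stands, and the point is therefore conditional on one order being used.

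A reader might also infer that the per-category results as a whole cannot be interpreted, or that the breadth rule is biased. The documents do not support either. The comparison of streams within a category is protected by randomisation. The breadth rule asks whether clouds widen suggestions, not which cloud does most. If respondents tire by the fourth page, the package really does deliver less there; that limits the intervention and does not confound the comparison.

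Three further objections carry part of their weight:

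- *No comparison between clouds is planned.* This is true of the stream comparison. It is not true of the competition correlation, which contrasts clouds by construction, nor of a pooled size correlation.
- *Overlap was removed.* It was removed in part only, as shown above.
- *Navigation is free.* The viewing order is therefore not strictly forced, but free movement does not balance it either.

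Finally, no drop-off is documented, so fatigue and loss are plausible rather than shown.

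**Conclusion.** The concern holds in a limited and conditional form. If all respondents see the clouds in one order, position is aliased with phase of care in three places: the competition correlation, the size correlation when pooled over clouds, and the before/after yields when compared between categories or attributed to a single cloud. The randomised between-stream results, overall and per category, are unaffected as estimates of the package as delivered, and so is a breadth judgement based on them.

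The size of the distortion is unknown. The range of 42% to 86% for the fourth cloud relative to the first rests entirely on assumed losses of 25% to 5% per page and equal true effects. Carry-over of shared themes could add to it but cannot be quantified from the documents. This is an inexpensive improvement to the secondary and exploratory readings and does not undermine the trial's randomised comparison.

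**What to change.** Before the survey opens:

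1. State the order in which the cloud pages are shown.
2. Randomise that order per respondent in the survey platform, or use a 4 × 4 Latin square, and store the position of each cloud.
3. Account for position in the word-size, competition and cross-category before/after results. Report the competition result with the caveat that it still rests on about four values, one per category.

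If a fixed order is kept, say so, limit per-category conclusions to between-stream effects of the package, and do not compare clouds with each other or credit questions to one of them.

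The cost is a page-order setting and a stored position for each cloud. The downside is that some respondents meet the phases of care in a less natural sequence. Rotation shares fatigue equally among the phases; it does not remove it.

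### Only the word-cloud stream is asked again, so both planned comparisons estimate clouds plus re-asking rather than the clouds alone

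*Protocol article*

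**What the plan says.** All of this is in the protocol article, section Implementation plan for AO Spine RECODE-DCM, unless another section is named.

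- **Allocation.** Within the PSP, "further 1:1 block randomization will occur to two streams, a survey including word clouds and a second stream without word clouds".
- **First pass.** "For those allocated to the word cloud stream, participants will complete the survey as planned initially".
- **Extra material, word-cloud stream only.** "after survey completion, respondents will be presented with a brief overview of the development method and aims of the word cloud subproject". Then: "Participants will then be presented with each word cloud in turn, with the option to submit further research questions". There are four clouds: diagnosis, treatment, long-term management and other.
- **No-cloud stream.** It is described only as lacking the clouds. Its stated use concerns back-editing. Because respondents can move freely until the last page, "it will be theoretically possible for participants in the word cloud stream to edit their pre-word cloud form having seen the word clouds", and the platform cannot track this. The plan answers that "by retaining an arm who have no access to the word clouds, any such cross over can be evaluated".
- **Comparisons.** The counts are questions submitted, questions in scope, and questions linked to a summary question on the final priority list. "These numbers will be compared between streams, and for those in the word cloud stream, before and after viewing the word cloud".
- **Claim to be supported.** The abstract hypothesizes that showing the patients' experience through word clouds will stimulate better-aligned questions. The implementation plan calls the clouds meaningful if they prompt broader suggestions across the phases of care. The Discussion sets out to evaluate whether the patient-generated clouds help the group develop questions.

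**The concern.** The streams differ in more than the clouds. One stream gets a second invitation for every phase of care and reads about the aims of the subproject; the other finishes after the standard survey. A respondent who is asked again may add a question whatever is on the page. Such additions would appear as a benefit of the clouds in both planned comparisons.

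What is at stake is attribution. If the result is positive, other priority-setting partnerships could adopt word clouds when a plain second invitation would have done as well. The missing control is a feature of the survey as configured, so no choice of test can supply it once the survey has closed.

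**Working it through.** **Plan's own figure.** There is none to reproduce. The article states no sample size, significance level, expected count or re-asking yield. The check is therefore of what each contrast estimates, followed by an illustration.

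**Step 1: what each contrast estimates.** Let F be the mean number of first-pass questions. Let R be the yield from the extra pages apart from the clouds (second invitation and overview). Let C be what the clouds add to that.

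- Between streams, all questions: (F + R + C) − F = R + C.
- Before/after within the word-cloud stream: (F + R + C) − F = R + C.
- Between streams, first form only (the article does not say which set is meant): this contains none of the answers given on the cloud pages and picks up only back-editing.

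None of the three equals C. The before/after contrast also has a fixed direction: if the after count is cumulative, it cannot fall for anyone who leaves the first form unedited.

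**Step 2: breadth.** Suppose, as an assumption, that breadth is the number of the four phases with at least one question. Re-prompting each phase can then raise it but cannot lower it, edits aside. A respondent already at 4 of 4 cannot rise further. The Introduction says the standard survey already has sub-sections for all four areas, so the room for a rise may be small. Its size is unknown.

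**Step 3: illustration with C = 0.** Every input is assumed: m = 4 first-pass questions per person, variance 2m = 8, re-asking adds a fraction r, n per stream, two-sided 5% normal test.

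- Difference: d = r·m
- SD (average variance of the two streams): √(2m(1 + r/2))
- SE = SD·√(2/n)
- P(reject) = Φ(d/SE − 1.96) + Φ(−d/SE − 1.96)

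Example, n = 100 and r = 0.20: d = 0.8; SD = √8.8 = 2.966; SE = 2.966 × √0.02 = 0.4195; d/SE = 1.907; P = Φ(−0.053) + Φ(−3.867) = 0.48.

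| n per stream | r = 0 | r = 5% | r = 10% | r = 20% | r = 30% |
|---|---|---|---|---|---|
| 50 | 0.05 | 0.06 | 0.11 | 0.27 | 0.51 |
| 100 | 0.05 | 0.08 | 0.16 | 0.48 | 0.80 |
| 200 | 0.05 | 0.11 | 0.28 | 0.77 | 0.98 |

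**Step 4: with a matched second pass.** Between streams, all questions: (F + R + C) − (F + R) = C. With C = 0 the expected difference is 0 and rejection returns to 5% whatever R is.

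**Step 5: which outcome to use after matching.** Suppose a fraction b of cloud-prompted questions is typed into the first form by back-editing. The second-pass contrast is then R + (1 − b)C − R = (1 − b)C. With an assumed C = 0.5, this is 0.50, 0.35, 0.20 and 0 for b = 0, 30%, 60% and 100%. Adjusting for the first-pass count does not repair this, because that count is itself affected by the clouds. The total count does not depend on where a question was typed, so its contrast stays at C.

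**The case against.** **The package reading.** The between-stream contrast is randomized and validly estimates the whole add-on, clouds plus second invitation, against the standard survey. That is arguably what a future partnership would adopt, and the article leaves the value of any impact to further research. This stands, but only for a conclusion worded about the package. The hypothesis and success criterion are worded about the clouds.

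**The no-cloud arm is already the control.** It is, for back-editing, which is the use the plan gives it. It does not control for re-asking.

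**Free movement.** The no-cloud stream may also be able to go back and add questions. It is not invited to, so opportunity remains unequal.

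**Word-size correlation.** The plan also relates the number of questions matching each word to its size and competition in the cloud. This bears on cloud content, so a reader should not infer that the study can say nothing about the clouds. But large words may simply be common topics, and this analysis provides no control for re-asking in the two comparisons at issue.

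**Overstatement.** A reader might infer that breadth is bound to rise. It can, but the standard survey already covers every phase, breadth is not defined as a count, and it was not modelled here. A reader might also cite a before/after test that is nearly always positive. That follows by construction from testing non-negative additions against zero, and the plan names no such test. Nor does the text say that respondents are told which result is hoped for; it mentions only the development method and aims.

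**Cost of matching.** Re-prompting the no-cloud stream could lead its members to edit their first forms too. This is a real loss, since preserving the traditional JLA method was one reason for the chosen sequence.

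**Conclusion.** The point holds in a limited form. As described, both the between-stream and the before/after comparison estimate clouds plus re-asking, so a gain in question counts or breadth cannot be credited to the clouds alone. This follows from the article's own account of the two streams and needs no numerical assumption beyond taking that account as complete: a second invitation to the no-cloud stream is neither described nor implied.

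The size of the bias is unknown. The rates in the table (0.06 to 0.98 for r from 5% to 30% and 50 to 200 per stream) rest wholly on assumed inputs. They show direction and range and do not forecast this study's error rate. A reader might infer that a positive result would be spurious; the documents do not support that, because the clouds may well add something. The design cannot separate the two.

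**What to change.** **If the survey can still be changed:**

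1. After the standard survey, show the no-cloud stream the same four follow-up pages, with the same wording and free-text boxes but no cloud.
2. Use the same neutral introduction in both streams and move the subproject's aims to the final page.
3. Base the conclusion on the between-stream comparison of total (first form plus follow-up) in-scope questions and breadth.
4. Report second-pass counts as secondary, since untracked back-editing makes them unreliable even after adjustment for first-pass counts. Report before/after as descriptive only.

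The cost is survey configuration, protocol wording and four optional extra pages for the no-cloud stream. That stream's first form could also be back-edited, so it would no longer be a wholly untouched traditional JLA arm.

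**If the survey cannot be changed, or that arm must be kept untouched:** restate the conclusion as the effect of a second pass with word clouds versus no second pass. This costs only wording but gives up the claim about the clouds themselves.

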## Abstract

**Objectives:**

AO Spine REsearch objectives and Common Data Elements for Degenerative Cervical Myelopathy [RECODE-DCM] is a multi-stakeholder consensus process aiming to promote research efficiency in DCM. It aims to establish the top 10 research uncertainties, through a James Lind Alliance Priority Setting Partnership [PSP]. Through a consensus process, research questions are generated and ranked. The inclusion of people with cervical myelopathy [PwCM] is central to the process. We hypothesized that presenting PwCM experience through word cloud generation would stimulate other key stakeholders to generate research questions better aligned with PwCM needs. This protocol outlines our plans to evaluate this as a nested methodological study within our PSP.

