**Results:**

Seventy-nine terms were submitted after the first poll. Eighty-seven refined words were then re-polled (which added a further 39 words). Four word clouds were generated under the categories of diagnosis, management, long-term effects, and other. A 1:1 block randomization protocol to assess word cloud impact on the number and relevance of PSP research questions was generated.

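### Relevance is a stated target, but the metrics that bear on it are counts that rise with volume, and only the word-cloud stream gets a further chance to submit

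*Protocol article*

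**What the plan says.** The Results paragraph of the abstract gives the purpose of the randomised comparison: "to assess word cloud impact on the number and relevance of PSP research questions". Number and relevance appear there as two attributes. The abstract's Objectives paragraph points the same way. Its hypothesis is that showing patients' experience "would stimulate other key stakeholders to generate research questions better aligned with PwCM needs", which concerns what kind of questions are produced and not only how many.

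The section Implementation plan for AO Spine RECODE-DCM lists three metrics and says that these counts are what the two streams will be compared on: "These numbers will be compared between streams, and for those in the word cloud stream, before and after viewing the word cloud". Two of the metrics are the total submitted and those judged in scope. The third looks further down the process, to the ranked output: "the number linked to a summary question appearing in the final research priority list, will be recorded in this evaluation". No share, rate or denominator is named.

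The same section describes the allocation: "further 1:1 block randomization will occur to two streams, a survey including word clouds and a second stream without word clouds". People in the word-cloud stream first complete the ordinary survey. After that, "Participants will then be presented with each word cloud in turn, with the option to submit further research questions". No comparable second invitation is described for the other stream.

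The section states one rule for calling the clouds meaningful, and it concerns how widely suggestions spread over the stages of care. The choice of test is left to the distribution of the data.

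**The concern.** Every in-scope question is also a submitted question, and so is every priority-linked one. A stream that submits more will therefore tend to have more of both, even if its questions are no more relevant. The design gives one stream an extra opportunity to submit, so a difference in volume is to be expected.

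A higher in-scope or priority-linked count in the word-cloud stream would then fit three situations: more relevant questions, equally relevant but more numerous questions, or less relevant but more numerous questions. The comparison as written cannot tell these apart. At stake is the relevance half of the stated purpose, because a volume effect could be read as a relevance effect.

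The before-and-after comparison within the word-cloud stream has the same weakness. If the later figure is cumulative, further submissions can only add to each count, apart from edits to earlier answers. If it covers only the added questions, it depends on how many people took up the option.

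**Working it through.** The article gives no sample size, question rate or expected effect, so there is no figure of its own to reproduce. The structure (three nested counts, 1:1 allocation, an extra submission step in one stream) comes from the Implementation plan. All rates below are assumptions.

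**General result.** Let the control stream submit N questions with relevant share s_c, and let the word-cloud stream submit vN with relevant share s_w. The relevant counts are N·s_c and vN·s_w. The word-cloud count is higher whenever

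v·s_w > s_c, that is, s_w > s_c / v.

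**Break-even shares.** The share in the word-cloud stream at which its count only equals that of control:

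| v | control 80% in scope | control 30% priority-linked (of submitted) |
|---|---|---|
| 1.2 | 0.80/1.2 = 66.7% | 0.30/1.2 = 25.0% |
| 1.4 | 0.80/1.4 = 57.1% | 0.30/1.4 = 21.4% |
| 2 | 0.80/2 = 40.0% | 0.30/2 = 15.0% |

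Any share above the break-even value makes the word-cloud count higher, even where it is below the control share.

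**Worked example.** Assume 5 questions per respondent in the ordinary survey in both streams, 80% in scope, so 5 × 0.80 = 4.0 in scope for control. Add 2 questions per respondent after the clouds (v = 7/5 = 1.4) and vary the in-scope share of those added:

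| Added questions in scope | In-scope count (control 4.0) | In-scope share (control 80%) |
|---|---|---|
| 80% | 4.0 + 1.6 = 5.6 | 5.6/7 = 80.0% |
| 60% | 4.0 + 1.2 = 5.2 | 5.2/7 = 74.3% |
| 40% | 4.0 + 0.8 = 4.8 | 4.8/7 = 68.6% |
| 20% | 4.0 + 0.4 = 4.4 | 4.4/7 = 62.9% |

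The count rises in every row, while the share is unchanged in the first and lower in the rest. If the added questions were more often in scope than the first ones, count and share would both rise. The count therefore points the same way throughout.

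**Priority-linked questions.** Assume 30% of the first 5 and 15% of the 2 added are linked, with 40% of the added ones in scope. The counts are 5 × 0.30 = 1.5 and 1.5 + 2 × 0.15 = 1.8, a rise of 20%. As a share of submitted questions this is 30% against 1.8/7 = 25.7%. As a share of in-scope questions it is 1.5/4.0 = 37.5% against 1.8/4.8 = 37.5%. So the count rises by a fifth with no change in that share.

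**What a test would show.** The 40% row was simulated with 2,000 runs and Poisson numbers of questions with means 5 and 2. A Mann-Whitney test on in-scope counts found the word-cloud stream significantly higher in 48%, 75% and 96% of runs with 50, 100 and 200 respondents per stream. A test of the in-scope share found it significantly lower in 88%, 99.6% and 100%. Questions were generated as independent within a person, so the figures for the share test are optimistic.

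**The case against.** The strongest reply is that these counts answer a question the study does ask. The Discussion wants to know whether the clouds help the group develop research questions, and priority ones in particular. That is yield. Out-of-scope suggestions are discarded in processing, so 0.8 extra in-scope questions per respondent (4.8 against 4.0) may be a real gain for a priority-setting exercise even if the in-scope share is lower. This stands, and it is the reason to keep the counts. It does not make them a measure of relevance.

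A second reply is that an article may leave the analysis model to a fuller document. That is right for the model and the test. The point here is different: the article itself fixes the metrics and says the numbers are what is compared.

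A reader might infer more than the text supports:

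- **That the plan declares relevance will be judged by raw counts.** It does not say so. The link follows from the stated purpose together with the absence of any other metric that bears on relevance.
- **That a fall in quality would be hidden.** The total is recorded beside the other two counts, so shares can be derived. They are simply not planned.
- **That the study's verdict on the clouds is compromised.** The only stated criterion for a meaningful result is breadth, which this point does not touch.
- **That the plan tests pooled questions as if independent, with inflated error rates.** No such test appears. The method is left open, and no test of proportions is planned at all.
- **That the clouds will lower relevance.** The document shows only that count and share can diverge.

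**Conclusion.** The point holds in a limited form. The abstract promises an assessment of relevance as well as number, but the metrics that bear on relevance are counts nested in the total, and one stream has an added opportunity to raise that total. A higher count cannot separate more questions from more relevant ones.

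The size depends on the unknown volume ratio. For ratios of 1.2 to 2, an assumed 80% in-scope share could drop to just above 66.7% down to just above 40% while the count still favoured the clouds. The direction follows from the design; the rates are illustrative. The consequence is confined to what may be concluded about relevance. It is worth correcting because the remedy needs almost nothing beyond wording.

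**What to change.** 1. Keep the three counts, analysed per randomised respondent with those who submitted nothing counted as zero. Label the total as volume, and the in-scope and priority-linked counts as yield.
2. Add two relevance measures: the in-scope share of submitted questions, and the priority-linked share of in-scope questions. Compare them between streams and, within the word-cloud stream, between questions entered before and after the clouds. The analysis should allow for several questions from one respondent.
3. State that any conclusion about relevance rests on the shares read together with the counts.

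The cost is a few sentences of analysis wording and some extra tabulation. The audit trail described in the Implementation plan already follows each submission, so no new data are needed.

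There is a downside. The first share exists only for respondents who submitted a question, and the second only for those with one in scope. Both conditions arise after randomisation, so the shares supplement the counts and do not replace them. Report, per stream, how many respondents submitted no question. The pre- versus post-cloud shares carry a further caution that the article itself gives: earlier answers can be edited after the clouds are seen, and the platform cannot track this.
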